### Sample size calculation and statistical analyses

Previous studies have observed an incidence of MAKE90 of 25% among patients that required elective cardiac surgery [38, 39]. Assuming the prior proportion of MAKE90 to be 25% for the placebo group, a sample size of 546 patients (273 patients per treatment group) will provide a 90% (β = 0.10) power to detect a statistically significant difference of 10% in the proportion of patients with MAKE90 under a one-sided significance level of 5% (α = 0.05), i.e. to detect a proportion of 15% for the empagliflozin group. Finally, by taking in account a potential dropout rate of 10% we determined a sample size of 608 patients (304 patients per treatment group).

Our trial will apply adaptive Bayesian methodology to estimate the proportions of patients with the primary endpoint in both groups. For such a purpose, a conjugate beta-binomial model will be used, allowing for continuous updates of posterior distributions as new samples are obtained. This means that, as additional data are collected, proportion estimates will be dynamically adjusted, providing a real-time view of treatment effectiveness in disease prevention.

Two interim analyses will be carried out by the independent data monitoring committee. These analyses will be carried out once 30% and 60% of the planned study sample have been recruited. The objective of the first analysis will be to assess the futility of the study intervention, using conditional power analysis. The aim of the second analysis will be to evaluate the need to adjust the study sample size. Both interim analyses will be performed by an external statistician to ensure that no loss of blinding occurs.

Primary endpoint analysis will be based on the intention-to-treat population, defined as all validly randomized patients. In the analysis of the primary endpoint, study treatments will be compared using a Cox proportional hazards regression model with a factor for the treatment group. Hazard ratio, 95% confidence interval and *P*-value will be reported. Kaplan–Meier estimates of the cumulative incidence to the occurrence of MAKE90 will be calculated. Secondary endpoints will be tested in a similar manner. If superiority is achieved for the primary endpoint, the secondary endpoints will be tested following a hierarchical order, as follows. (i) Any stage of AKI defined according to Kidney Disease: Improving Global Outcomes (KDIGO) guidelines during index admission. (ii) Stage 3 AKI according to KDIGO guidelines during index admission. (iii) Time to renal replacement therapy initiation during index admission. (iv) Time to death from any cause. Statistical significance will be required before testing the next hypothesis in the hierarchy. The effects of the planned intervention on primary and secondary outcomes will also be assessed in subanalyses stratified by sex, baseline eGFR, diabetic status and type of planned surgery (valvular/coronary/valvular and coronary).

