Several studies have observed incidence rates of MAKE90 in cardiac surgery patients of approximately 25% [38, 39]. A sample size of 608 patients will provide power of 90% to demonstrate a 10% reduction in the incidence of MAKE90 with empagliflozin versus placebo. This proportion has been chosen as it has been considered potentially achievable after reviewing the preclinical data and results of previously conducted trials on the subject, in addition to considering it as a clinically significant reduction [28, 44, 45]. Due to the existing limitations in relation to previous data, two interim analyses have been planned to evaluate futility and the need for a sample size re-estimation, applying adaptive Bayesian methodology. Results of the interim analyses will be reviewed by an independent data-monitoring committee, who will provide a recommendation to stop the trial early due to futility or to maintain or increase the sample size. All research team members, as well as participants, will remain blinded until study completion.

The primary endpoint of the study will be the incidence of MAKE during the first 90 days after surgery. This endpoint has been considered as a clinically meaningful tool that may help to increase our capacity to understand AKI in a wide variety of clinical settings, as well as providing a composite to allow comparison of potential interventions [47]. MAKE90 combines worsened renal function, defined as a decline in eGFR of ≥25%, new dialysis or death, thus including new-onset or progressive renal dysfunction of variable intensity, as well as death as the definitive major morbid outcome. A renal composite such as MAKE90 allows assessment of renal disability-free survival, securing a higher proportion of patients that suffer poor renal outcomes, in addition to eliminating potential competing risks [47].

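### The stated 90% power holds only for a one-sided 5% test, but the primary result is reported with a 95% confidence interval; at two-sided 5% power is about 83% to 88%

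*Protocol article*

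**What the plan says.** All of the following is in the Protocol article.

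- **Sample size calculation and statistical analyses, planning paragraph.** The test level is set "under a one-sided significance level of 5" per cent. The other inputs are "Assuming the prior proportion of MAKE90 to be 25% for the placebo group", and the aim is "to detect a proportion of 15% for the empagliflozin group". On that basis "a sample size of 546 patients (273 patients per treatment group") "will provide a 90% (β = 0.10) power". A 10% dropout allowance raises the total to 608 (304 per group).
- **Same section, analysis paragraph.** The primary endpoint is compared with a Cox model in all validly randomized patients. "Hazard ratio, 95% confidence interval and" a P-value are to be reported. Four secondary endpoints are tested in fixed order if superiority is shown on the primary, each needing statistical significance before the next. No level or sidedness is attached to any of these tests.
- **Discussion.** "A sample size of 608 patients will provide power of 90" per cent, with no mention that this rests on a one-sided test.

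**The concern.** By convention a 95% confidence interval is two-sided. It excludes a hazard ratio of 1 in the favourable direction only when the one-sided P-value is below 2.5%. A one-sided 5% test matches a 90% interval. The article therefore sizes the trial on one criterion and presents the result on another, without saying which decides.

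Two readings are open, and each has a cost:

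- If the 95% interval and a conventional two-sided P-value decide, power is lower than the article states.
- If one-sided 5% decides, the false-positive rate in the favourable direction is 5%, twice what the reported interval implies. A trial declared positive could then carry an interval that includes no effect.

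For results between the two thresholds, the choice could be made after the data are known. The same decision opens the four-step hierarchy. It also bears on the first interim analysis, because conditional power for futility is computed against the final critical value, and 1.645 and 1.960 give different answers.

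**Working it through.** **Inputs.** From the sample size section: p1 = 0.25, p2 = 0.15, power 90%, one-sided α = 0.05, 273 per group, 10% dropout. Allocation is 1:1 (Randomization, stratification and blinding). Normal quantiles: 1.645 (one-sided 5%), 1.960 (two-sided 5%), 1.282 (90% power).

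**1. Reproduce the plan's figure.** The pooled two-proportion formula, with p̄ = 0.20, is

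n = [z_α √(2p̄(1−p̄)) + z_β √(p1(1−p1) + p2(1−p2))]² / (p1−p2)²

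Here √0.32 = 0.5657 and √(0.1875 + 0.1275) = 0.5612.

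- One-sided 5%: (0.9305 + 0.7193)² / 0.01 = 272.2, so 273 per group and 546 in all. Then 273/0.9 = 303.3, so 304 per group and 608. Both match the article.
- Two-sided 5%: (1.1087 + 0.7193)² / 0.01 = 334.2, so 335 per group.

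The published number therefore comes from the one-sided 5% test.

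**2. Power at the planned size.** Power = Φ{[0.10√n − z_α × 0.5657] / 0.5612}.

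- n = 273: (1.6523 − 0.9305)/0.5612 gives 90.1% one-sided; (1.6523 − 1.1087)/0.5612 gives 83.4% two-sided.
- n = 304, nobody lost: 92.6% one-sided, 87.1% two-sided.

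Exact enumeration of the same z test at 273 per group, two-sided, gives 83.7%. Continuity correction or Fisher's exact test gives 80.5% to 80.9%.

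**3. Power on the scale of the planned Cox analysis.** This assumes proportional hazards, which the article does not quantify: HR = ln 0.85 / ln 0.75 = 0.565, so |ln HR| = 0.571. Expected events are 273 × (0.25 + 0.15) = 109.2, or 304 × 0.40 = 121.6. Power = Φ(|ln HR| √(D/4) − z_α).

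| | One-sided 5% | Two-sided 5% |
|---|---|---|
| Proportions, 273 per group | 90.1% | 83.4% |
| Proportions, 304 per group | 92.6% | 87.1% |
| Cox, 109 events | 91.0% | 84.7% |
| Cox, 122 events | 93.4% | 88.3% |

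Every two-sided figure is below 90%.

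**4. Results on which the two rules disagree.** With 25% observed on placebo and 273 per group, the smallest significant difference solves d = z√(2p̄(1−p̄)/n) with p̄ = 0.25 − d/2. This gives 5.84 points one-sided and 6.90 points two-sided. On the Cox scale the thresholds are exp(−2z/√109.2), that is 0.73 and 0.69. A result between them passes the one-sided test while its 95% interval includes no effect.

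The chance of landing in that band is the gap in power: 90.1 − 83.4 = 6.7 percentage points at 273 per group, or 92.6 − 87.1 = 5.5 at 304, under the design alternative. With no true effect it is 5 − 2.5 = 2.5%.

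**The case against.** The strongest reply is that the article states only one significance level, openly, and that its calculation is correct at that level. Superiority and statistical significance in the analysis paragraph can be read as referring back to it. The 95% interval is only to be reported; nothing says it decides, and the P-value is never called two-sided. A condensed article may also leave the sidedness of each test to the full protocol or analysis plan, and a Discussion sentence need not repeat every condition. Finally, 83% is the low end: the primary analysis includes all randomized patients, and those lost contribute until censoring, so the two-sided figure could reach 87% to 88%.

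Several of these points stand. The two-sided reading is convention, not text. The sample size contains no arithmetic error. The power loss is a range, and it stays above 80%. A one-sided level disclosed in advance is a legitimate design choice.

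They do not remove the mismatch. The article fixes both a one-sided 5% design level and a 95% interval, and these do not correspond. If one-sided 5% was meant to decide, the accompanying interval is not the matching one. If the interval was meant to decide, the stated power is too high. The 90% in the Discussion, read alone, will be taken as power for a conventional test. These are things the article states, so they do not depend on what an unseen analysis plan may add.

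**Conclusion.** The concern holds. The planning rule (one-sided 5%) and the reported inference (95% interval) are different success criteria, and the article does not say which one governs. If two-sided 5% governs, power for 25% versus 15% is 83.4% with 546 evaluable patients and 87.1% with all 608, or 84.7% and 88.3% on the Cox scale under proportional hazards. If one-sided 5% governs, the 90% is right, but observed reductions of about 5.8 to 6.9 points (HR about 0.73 to 0.69) would be declared superior with a 95% interval that includes no effect. These figures rest on the article's own event rates. The band also assumes 273 evaluable per group and, in points, 25% observed on placebo.

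**What to change.** State one level and sidedness for the primary superiority test and for each step of the hierarchy, before any unblinded interim result is seen, and use the same critical value in the conditional power calculation.

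- **Preferred:** a two-sided 5% test, with the 95% interval already planned. Restate the power in the sample size section and in the Discussion as about 83% with 546 evaluable patients, rising to about 87% if all 608 contribute.
- **Alternative:** keep one-sided 5%. Say so for the primary test, for every hierarchical test and beside the 90% in the Discussion, and name the 90% interval as the decision interval. A 95% interval can still be shown as description.

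Either option costs wording; the first also costs a less favourable stated power. Enrolment need not change. Keeping 90% power at two-sided 5% would be a separate decision: it needs 335 per group evaluable, and 335/0.9 = 372.2, so 373 per group and 746 in all, 138 more than planned.

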### Outcome definitions and background medication

The primary endpoint of the study will be the time to the first occurrence of any major adverse kidney event during the first 90 days after surgery (MAKE90). The components of MAKE90 will be a ≥25% eGFR decline from preoperative baseline, the start of renal replacement therapy or patient death. Secondary, tertiary and safety endpoints are listed in Table 2. Treating physicians will be responsible for adjudicating possible postoperative complications.

**Table 2: tbl2:** Primary, secondary, tertiary and safety endpoint of the VERTIGO trial.

Primary endpoint
Proportion of patients that present MAKE90, defined as one or more of the following:
- ≥25% eGFR decline from preoperative baseline
- Start of renal replacement therapy
- Patient death
Secondary endpoints
- Proportion of participants who developed any stage of AKI defined according to KDIGO guidelines during index admission
- Proportion of patients who suffered a Stage 3 AKI according to KDIGO guidelines during index admission
- Proportion of patients who required renal replacement therapy during index admission
- Proportion of patients who died during index admission
- Proportion of patients that maintain ≥25% eGFR decline from preoperative baseline 90 days after surgery
Tertiary endpoints
- Difference in total time (h) on mechanical ventilation
- Difference in mean daily dose of inotropes used
- Difference in plasma levels of interleukin-6 and C-reactive protein
- Difference in urinary levels of interleukin-18 and protein/creatinine ratio
- Difference in serum interleukin-1β and interleukin-18 concentration
- Time to first occurrence of postoperative complications, defined as low cardiac output, reoperation for bleeding, delirium, seizures, surgical site infection, sepsis, arrhythmias, cardiac arrest, pneumonia, liver dysfunction or need for blood transfusion
- Difference in total time (days) spent in the ICU
- Difference in total time (days) of index hospital stay
- Difference in rates of hospital readmission due to cardiovascular disease
- Difference in frailty evaluation, represented by the results of the Clinical Frailty Scale
- Patient reported quality of life EuroQoL-5D
Safety endpoints
- Adverse events
- Serious adverse events (i.e. adverse event that results in death, is considered life-threatening, requires or extends an hospitalization episode, causes disability or is judged as such according to the clinical criteria of the research team)

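### In-admission renal replacement therapy is a proportion in Table 2 but a time-to-event test at step (iii) of the hierarchy; the two can disagree if treatment changes length of stay

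*Protocol article*

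**What the plan says.** Table 2 (Outcome definitions and background medication) lists the secondary endpoint as "Proportion of patients who required renal replacement therapy during index admission". The two AKI endpoints during the index admission are also listed there as proportions.

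Under Sample size calculation and statistical analyses, the primary comparison is specified thus: "study treatments will be compared using a Cox proportional hazards regression model with a factor for the treatment group". The section continues: "Secondary endpoints will be tested in a similar manner". The third hypothesis in the hierarchy is then "iii) Time to renal replacement therapy initiation during index admission", and the fourth is time to death from any cause, without the limit to the admission. On gatekeeping: "Statistical significance will be required before testing the next hypothesis in the hierarchy".

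Three further statements bear on the point:
- Kaplan–Meier is mentioned once, for the primary endpoint: "Kaplan–Meier estimates of the cumulative incidence to the occurrence of MAKE90 will be calculated".
- The Discussion credits the composite primary endpoint with "in addition to eliminating potential competing risks". No corresponding handling is given for RRT alone.
- Table 2 has a tertiary endpoint "Difference in total time (days) of index hospital stay", so the plan allows that treatment may change the time of discharge.

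**The concern.** One confirmatory endpoint has two forms. Table 2 asks what share of patients needed RRT before leaving hospital. The hierarchy asks how the rate of starting RRT compares between arms, presumably as a hazard ratio.

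The two part company because an event that counts only during the admission cannot occur after discharge. In an ordinary Cox analysis, a patient without RRT would leave the risk set at discharge or death. The hazard is then taken over those still in hospital. If one arm goes home sooner, the same number of RRT starts is divided by fewer patient-days and the hazard ratio moves, although the proportions are equal. A shorter stay on the drug works against it; a longer stay works in its favour.

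At stake is which answer counts at step (iii), and so whether death is tested at all.

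**Working it through.** **Inputs from the article.** 304 patients per arm and a one-sided 5% level, both from the sample size paragraph. The size reproduces: with 25% v 15% and 90% power, n = [1.645·√(2·0.20·0.80) + 1.282·√(0.25·0.75 + 0.15·0.85)]² / 0.10² = (0.931 + 0.719)² / 0.01 ≈ 272.2, so 273 per arm, and 273/0.90 = 303.3, so 304. The article gives no figure for RRT.

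**Assumptions.** RRT rate, RRT timing, length of stay and, in step 1, death rate. Censoring at discharge and death is also an assumption.

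**Step 1: closed form.** Take constant daily hazards a (RRT), d (discharge) and m (death). The in-admission proportion is p = a/(a + d + m), so a = p(d + m)/(1 − p). With equal p in both arms, the hazard ratio is (d₁ + m)/(d₀ + m). With m = 0.003:
- Mean time to discharge about 10 v 8 days (d = 0.100 v 0.125): 0.128/0.103 = 1.24.
- About 10 v 6.7 days (d = 0.100 v 0.150): 0.153/0.103 = 1.49.
- Conversely, with equal RRT hazards and p = 3% in the control arm, a = 0.03·0.103/0.97 = 0.0032. The hazard ratio is 1.0, but the risk ratio is 0.1062/0.1312 = 0.81.

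Constant hazards spread RRT over the whole stay, so this is a late-RRT case. In simulation (two-sided 5%), equal proportions were rejected in 7.9% (RRT 3%) and 9.2% (RRT 5%) of trials at 10 v 8 days, and in 18.1% (RRT 5%) at 10 v 6.7 days. The two-proportion test, and a test keeping patients without RRT at risk to day 90, stayed at 4.5% to 5.4%.

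**Step 2: a smaller difference in stay, with RRT timing varied.** Lognormal stay (log-SD 0.5), median 8 days on placebo and 8 or 7 on the drug. RRT time is lognormal: late is median day 5 (log-SD 0.8); early is median day 2 (log-SD 0.6) or day 3 (log-SD 0.5). No deaths; 4,000 trials per scenario; one-sided 5% log-rank test censoring at discharge.

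| Scenario | Late RRT | Early RRT |
|---|---|---|
| Equal RRT (3% or 5%), equal stay: rejection in favour of drug | about 5% | about 5% |
| Equal RRT, stay 7 v 8: hazard ratio | about 1.17 (1.15 to 1.19 across runs) | 1.02 to 1.05 |
| Equal RRT, stay 7 v 8: rejection for / against drug | 2–3% / 10–11% | 4–5% / about 6% |
| RRT 5% v 2%, stay 7 v 8: power, proportion test | about 65% | 64–65% |
| RRT 5% v 2%, stay 7 v 8: power, censoring at discharge | about 51% | about 62% |

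Keeping discharged patients in the risk set event-free to day 90 gave the same power as the proportion test.

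**The case against.** The strongest reply is that the article never says patients are censored at discharge. Patients are followed to day 90 for the primary endpoint, so a Cox model that keeps discharged patients event-free fits the text as well and shows none of these effects. Such a rule commonly sits in an analysis plan that is not shown. This stands: the censoring is an inference, and its absence from an article is not an error. It does not remove the conflict of form, since the article itself names both the proportion and the time to event.

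A reader might go further and infer that the cumulative incidence of RRT will be grossly overstated. The article does not support that. Kaplan–Meier is named for MAKE90 only. A day-30 curve under such assumptions would also rest on almost nobody: with median stay 8 days and log-SD 0.5, the share still in hospital is P(Z > ln(30/8)/0.5) = P(Z > 2.64) ≈ 0.4%, or about 1.3 of 304 patients.

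Nor is the test invalid in general. With censoring at discharge it remains a valid test of the cause-specific hazard and holds its level when stay is equal. It misleads about the proportion only if treatment changes stay (or death), and listing stay as a tertiary endpoint does not show that it will. Finally, the step is reached only after the primary endpoint and both AKI steps succeed.

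**Conclusion.** The point holds as an inconsistency with a conditional consequence. The same confirmatory endpoint is a proportion in Table 2 and a time to event in the hierarchy, and the two can give different answers.

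The size depends on three things that the article does not fix: whether patients are censored at discharge, whether treatment changes stay, and when RRT starts. A one-day difference in median stay does almost nothing if RRT is early. If it is late, it costs about 14 points of one-sided power (65% to 51%) for a true 5% v 2%. Larger differences in stay with late RRT do more. By symmetry, a longer stay on the drug would bias the hazard ratio in its favour.

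The unconditional reading, that the planned analysis distorts both estimate and test, is not supported. The primary analysis and the 608 patients are unaffected. The choice still matters because step (iii) decides whether death is tested.

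**What to change.** Test step (iii) as the Table 2 proportion: RRT yes or no during the index admission, in all randomised patients, with a risk difference or ratio stratified by site and diabetic status. Reword the hierarchy to match.

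If a time-to-event analysis is preferred, state that discharged patients remain in the risk set as event-free to day 90 and that death is a competing event.

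Make the same choice explicit for AKI steps (i) and (ii). Table 2 lists them as proportions and the hierarchy does not word them as times, but the general sentence on secondary endpoints covers them.

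The cost is wording, settled before unblinding; no new data or patients are needed. Replacing the admission by a fixed 30- or 90-day window would be a larger step, because it changes the stated endpoint, and it is not needed here.

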## DISCUSSION

VERTIGO is designed as a Phase 3, investigator-initiated, randomized, double-blind, placebo-controlled, multicenter study that will examine whether empagliflozin added to standard care for patients that undergo elective cardiac surgery reduces the incidence of MAKE up to 90 days after surgery.

CSA-AKI is a common complication that occurs in approximately 20%–40% of patients that require cardiac surgery [40]. Its incidence is expected to increase in the coming years due to progressive changes in the profile of these patients, who are older and suffer greater comorbidities. Multiple perioperative strategies have been implemented to reduce the incidence of kidney-related adverse events associated with cardiac surgery. These include pharmacological, technical and management-related interventions, performed pre-, intra- and/or postoperatively [40]. Published trials and meta-analyses are characterized by a marked lack of homogeneity in renal outcomes definition, timing of planned intervention as well as length of follow-up.

Certain interventions, such as perioperative sodium bicarbonate, n-acetylcysteine, dexmedetomidine or remote ischemic preconditioning have proved ineffective [8, 41, 42]. In addition, several randomized controlled trials have offered conflicting results regarding actual efficacy of specific interventions, like the administration of erythropoietin or levosimendan [7, 43, 44]. Additional controlled trials that were studying potential treatment alternatives, such as hemoperfusion with CytoSorb during ECC (NCT3384875) or teprasiran (NCT03510897), were terminated early due to either undisclosed reasons or to results not meeting efficacy outcomes at the prespecified time point.

As a result, no preventive or therapeutic strategy for CSA-AKI, outside of hemodynamic, respiratory and nutritional support, has managed to effectively translate so far into daily clinical practice, while morbidity and mortality remain significantly increased not only in the acute postoperative period but also in the ensuing years after surgery, generating index hospitalization-associated costs of approximately US ${\$}$1.01 billion annually in the USA [45, 46]. In this study we seek to test the potential of perioperative empagliflozin in preventing CSA-AKI and MAKE90.

Several studies have observed incidence rates of MAKE90 in cardiac surgery patients of approximately 25% [38, 39]. A sample size of 608 patients will provide power of 90% to demonstrate a 10% reduction in the incidence of MAKE90 with empagliflozin versus placebo. This proportion has been chosen as it has been considered potentially achievable after reviewing the preclinical data and results of previously conducted trials on the subject, in addition to considering it as a clinically significant reduction [28, 44, 45]. Due to the existing limitations in relation to previous data, two interim analyses have been planned to evaluate futility and the need for a sample size re-estimation, applying adaptive Bayesian methodology. Results of the interim analyses will be reviewed by an independent data-monitoring committee, who will provide a recommendation to stop the trial early due to futility or to maintain or increase the sample size. All research team members, as well as participants, will remain blinded until study completion.

The primary endpoint of the study will be the incidence of MAKE during the first 90 days after surgery. This endpoint has been considered as a clinically meaningful tool that may help to increase our capacity to understand AKI in a wide variety of clinical settings, as well as providing a composite to allow comparison of potential interventions [47]. MAKE90 combines worsened renal function, defined as a decline in eGFR of ≥25%, new dialysis or death, thus including new-onset or progressive renal dysfunction of variable intensity, as well as death as the definitive major morbid outcome. A renal composite such as MAKE90 allows assessment of renal disability-free survival, securing a higher proportion of patients that suffer poor renal outcomes, in addition to eliminating potential competing risks [47].

Secondary endpoints will provide additional information on the effect of empagliflozin on the incidence of AKI immediately after cardiac surgery. The use of KDIGO consensus criteria for AKI, a classification that employs serum creatinine levels as well as urine output to classify AKI severity [48], will allow for easier comparison of efficacy across different therapeutic strategies. The description of the effect of the planned intervention on kidney function will be completed with urinary biomarkers of AKI such as interleukin-18 or DKK3/albumin ratio. The results of secondary endpoints, in combination with the primary endpoint of the study, will provide an extensive exploration of the efficacy of empagliflozin in preventing CSA-AKI in the study sample using clinically meaningful outcomes.

Tertiary endpoints, such as time on mechanical ventilation after surgery, average inotrope dose, biomarkers of inflammation and AKI, frailty assessment, incidence of postoperative complications, as well as total length of intensive care unit and hospital stay, or need for hospital readmission for cardiovascular disease, will allow us to analyze the short- and medium-term postoperative recovery of patients.

The study will also provide information on the safety of perioperative empagliflozin in patients that require elective cardiac surgery. The safety profile of SGLT2i, and specifically empagliflozin, has been extensively described in recent years, both in patients with diabetes as well as in non-diabetic chronic kidney disease [25, 49, 50]. Empagliflozin is generally well tolerated, and specific potential complications, such as symptomatic dehydration, hypoglycemia or urinary tract infections, will be carefully monitored and reported throughout the trial.

Although multiple interventions have been tested aiming to reduce the incidence and severity of CSA-AKI, no treatment strategy has been successfully translated into daily clinical practice. Therefore, our study will be placebo controlled. All participants in the study will receive standard treatment as per treating physicians and local practice guidelines. Randomization will be stratified by center and diabetic status. To minimize the risk of selection bias, block randomization with random block sizes will be employed.

In summary, this trial will provide evidence about the efficacy and safety of empagliflozin in reducing the incidence and severity of CSA-AKI in patients that require elective cardiac surgery. To accomplish this task, we will use a Phase 3, investigator-initiated, randomized, double-blind, placebo-controlled, multicenter design, using standard care in both study groups and analyzing clinically relevant primary, secondary and tertiary endpoints. Interim analysis will be conducted with the purpose of assessing early futility and the need for sample size adjustment. Patient recruitment is expected to start in May 2024.

